## Methods

### Study design

This is a prospective, single-blind, randomized controlled clinical trial with hidden assignment and intent-to-treat analysis. We will recruit 76 patients with upper extremity motor deficits after stroke in convalescence and then randomly and equally assign them to LF-HF-rTMS, low-frequency, high-frequency, and sham stimulation groups. Subjects will be assessed for clinical behavior, neurophysiology, and serologic testing at baseline and after 2 weeks; further follow-up assessment of clinical behavior will be performed after 6 weeks (Fig. 1).

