### Sample size

We have calculated the sample size using the PASS 15 software. A literature search was conducted using FMA-UE as the primary indicator [8], specified as a two-sided test with *α* = 0.05 with a degree of certainty (test efficacy1-β) of = 0.8, and a total sample size of *N* = 60 cases was calculated. Considering a 20% dropout rate and the average distribution of each group, the total sample size was 76, with 19 individuals included in each group.

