### Data analysis

Data analysis will be performed by the SPSS 26.0 statistical software, and statistical analysis of efficacy will be based on intention-to-treat analysis (ITT) principles.We will check whether the data is normally distributed using the Shapiro Wilk normality test. Nonparametric analysis such as chi-square test will be applied for the count data, and it will be expressed as rate or composition ratio. Nonnormal data will be tested using the Kruskal–Wallis test.Paired *t*-tests will be used for pre- and post-treatment comparisons of groups, one-way ANOVA for inter-group comparisons, and Bonferroni correction for post hoc comparisons between groups.Two-factor repeated measures ANOVA will be employed to investigate the impact of within-group factors (time points) and between-patient factors (subgroups) on outcomes and to analyze main and interaction effects.Pearson correlation analysis will be performed to investigate the correlation between cortical excitability (latency and CMCT) and motor function (FMA), the relationship between serum factors (BDNF, proBDNF, and MMP-9) and motor function, and the correlation between cortical excitability and serum factors.

A *P* value of < 0.05 will be regarded as statistically significant.

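### The repeated-measures ANOVA named for the group-by-time effect needs complete rows, so without prior imputation the three-visit FMA-UE model falls short of the promised intention-to-treat analysis

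*Protocol article*

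**What the plan says.** The Study design section describes a "randomized controlled clinical trial with hidden assignment and intent-to-treat analysis". The Data analysis section repeats the commitment: "statistical analysis of efficacy will be based on intention-to-treat analysis (ITT) principles".

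The same section then names the methods. For group and time together: "Two-factor repeated measures ANOVA will be employed to investigate the impact of within-group factors (time points) and between-patient factors (subgroups) on outcomes". This is the only named method that estimates the group-by-time interaction. Of paired t-tests it says that such "tests will be used for pre- and post-treatment comparisons of groups, one-way ANOVA for inter-group comparisons", with Bonferroni-corrected post hoc comparisons. On software: "Data analysis will be performed by the SPSS 26.0 statistical software".

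On visits, Study design says: "Subjects will be assessed for clinical behavior, neurophysiology, and serologic testing at baseline and after 2 weeks". Only the clinical scales, FMA-UE among them, are assessed again at week 6.

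The Sample size section bases the calculation on FMA-UE, obtains 60 patients and raises this to 76: "Considering a 20% dropout rate and the average distribution of each group". It does not say when the losses are expected.

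**The concern.** Classical two-factor repeated-measures ANOVA, as run in the SPSS general linear model procedure, takes one row per patient with all visits filled. A patient with one empty visit leaves the model altogether. The plan expects one patient in five to be lost, so the promised population and the named model do not fit together unless something is done to the data first.

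FMA-UE is the exposed outcome: it is the basis of the sample size and the only one of the three primary outcomes with three visits. According to the Recruitment section, the inpatient stay lasts 2 weeks, so week 6 is a return visit. A patient who does not return still has a score from the end of treatment, and the three-visit ANOVA would throw it away. If leaving is related to how well the patient had done by week 2, the remaining patients give a biased comparison, although the data that would correct much of this were collected.

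**Working it through.** **Inputs.** From Sample size: 60 patients before dropout, 20% dropout, 76 in total, 19 per arm. From Study design: FMA-UE at baseline, week 2 and week 6; latency and BDNF at baseline and week 2 only. From Data analysis: the named tests. The timing of loss is not given, so it is varied below.

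**1. The plan's own figure.** 60 / (1 − 0.20) = 75, rounded up to a multiple of four arms = 76 = 4 × 19. This reproduces the stated total. (The alternative 60 × 1.2 = 72 does not.) The 60 itself cannot be reproduced, because the article gives no effect size, standard deviation or test for it.

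**2. Complete cases.** 76 × 0.8 = 60.8, about 61 patients, or 19 × 0.8 = 15.2 per arm. Patients without complete data: 76 × 0.2 = 15.2, about 15.

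**3. Patients used by each procedure, with nothing imputed.**

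| Share of the 15 losses before week 2 (assumed) | Baseline to week-2 paired t-tests, all arms together; week-2 one-way ANOVA | Three-visit repeated-measures ANOVA | Observed week-2 scores discarded by the latter |
|---|---|---|---|
| None | 76 | 61 | 76 − 61 = 15 |
| Half | about 68 | 61 | 68 − 61 = 7 |
| All | 61 | 61 | 0 |

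Latency and BDNF follow the second column, since they have no third visit to miss.

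**4. Precision.** If all loss comes after week 2, the week-2 standard error in the complete-case model is larger by a factor √(1/0.8) = 1.118, about 12%. With earlier loss the penalty is smaller. Planned power is not reduced: about 61 completers is what the calculation for 60 counted on.

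**5. Bias.** This depends wholly on why patients leave. All the illustrations below assume a rule for this.
- *Loss unrelated to outcome:* completers are unbiased. With no true effect, correlation 0.7 between visits and 20% loss after week 2, the simulated difference in change at week 6 was 0.00 SD.
- *Poor early gainers leave one arm, good early gainers leave another* (same settings, no true effect): a spurious difference of about 0.15 SD at week 6.
- *True effect 0.50 SD, about 19–20% overall loss after week 2, poor early gainers leaving the control arm more often* (correlation 0.7, baseline-adjusted): completers give 0.32 to 0.38 SD at week 2 and 0.43 to 0.45 at week 6. Using all observed data gives 0.50 at both.
- *True effect 0.50 SD, 20% loss, poor gainers leaving by the same rule in both arms* (logistic slopes 0.5, 1 and 2 per SD): completers give 0.48, 0.45 and 0.38 SD at week 2.

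Across the last two sets the week-2 estimate runs from about 0.32 to 0.48 SD against a true 0.50.

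**The case against.** The strongest reply is that no contradiction is written down. Repeated-measures ANOVA after imputation can honour intention-to-treat. The article nowhere says that patients with missing visits are excluded, and an imputation rule is commonly left to a full protocol or analysis plan, neither of which is shown. This stands: the absence of a missing-data rule is not itself a fault here, and the count of 61 holds only if nothing is imputed.

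A reader might infer that the whole analysis is therefore completers-only. The documents do not support that. The article names one-way ANOVA for comparing groups. Run at week 2, it keeps every patient with a week-2 score, as the baseline to week-2 paired t-test does. Two of the three primary outcomes, latency and BDNF, lose nothing through a missed week 6.

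It is also fair to say that the timing of loss is an inference. The article describes measures against it: follow-up fees and transport are reimbursed, and participants are reminded of visits. Patients do not know whether they receive sham, which makes strongly arm-dependent leaving less likely.

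What remains is narrower. The one method named for the group-by-time effect makes the promised population depend on an imputation step that the article does not mention, while an equally available method does not need it.

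**Conclusion.** The point holds for the three-visit FMA-UE model. Without prior imputation, and at the plan's 20% dropout, that model uses about 61 of 76 randomised patients and drops up to about 15 observed week-2 scores, depending on when patients leave. This does not match the intention-to-treat commitment made twice in the article.

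The consequence concerns the analysed population and possible bias, not planned power. The bias may be zero. Under the assumed outcome-related dropout rules above it took a true 0.50 SD to between 0.32 and 0.48 SD at week 2. A reader might infer that the effect would be halved; that needs strong selection and 25% missing, more than the plan expects, and nothing in the documents points to it.

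This is a cheap improvement to one named analysis, not a defect that must be cured before the trial can be interpreted.

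**What to change.** For FMA-UE, replace the two-factor repeated-measures ANOVA with a likelihood-based linear mixed model (SPSS MIXED) fitted to all observed visits, with arm, visit, arm-by-visit and an unstructured covariance matrix. Choose one treatment of baseline and state it:
- baseline as a response, so that every randomised patient with a baseline score contributes; or
- baseline as a covariate, with a statement that patients with no post-baseline score do not contribute.

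Take the between-arm contrasts from this model, and add a sensitivity analysis for departures from missing at random.

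The cost is a change of wording before unblinding and slightly more analysis work, with no new data and no new software. The model relies on missing at random, which the data cannot confirm; hence the sensitivity analysis.

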### Secondary outcomes

The National Institute of Health Stroke Scale (NIHSS) is used to evaluate the neurological function state of patients with stroke. This scale includes 11 items. The total score ranges from 0 to 42 points; and the higher the score, the more severe the nerve injury [26].The Brunnstrom staging (BS) scale for assessing movement function improvement in stroke patients. It is divided into stages I–VI; the greater the staging, the superior the restoration of function.Modified Ashworth scale (MAS) to evaluate variations in the patient’s muscle tone on a scale of 0, 1, 1 + , 2, 3, and 4 [27]; the higher the grade, the greater the muscle tone.The Modified Barthel Index (MBI) will be administered to the assessment of activities of daily living [28]. The total score is 100; a score ≤ 50 is classified as severe functional impairment, 50–75 as moderate functional impairment, 75–100 as mild functional impairment, and > 100 as no functional impairment.Central motor conduction time (CMCT) refers to the conduction time from the cerebral cortex to the alpha motor neurons in the anterior horn of the spinal cord. An intensity stimulus of 90% RMT will be applied to the patient’s seventh cervical spine (C7), and transmission time from C7 to the thumb short abductor muscle will be measured to calculate the difference between the transmission time from the scalp to the electrode piece and the transmission time from C7 to the electrode piece [29].Measuring serum biomarkers: the human MMP-9-ELISA kit (produced by ABclonal, China) will be used to quantify the level of MMP-9 expression in peripheral blood, and a human ProBDNF-ELISA kit (Biosensis, USA) will be used to detect the peripheral blood ProBDNF factor concentration [25]. The same protocol will be used to detect BDNF.

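### Brunnstrom and modified Ashworth grades are ordered, but the named pre/post and group-by-time analyses are numeric only, and the one rank test between arms leaves out the baseline grade

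*Protocol article*

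**What the plan says.** The Secondary outcomes section of the protocol article defines both scales as ordered grades. On BS it says: "It is divided into stages I–VI; the greater the staging, the superior the restoration of function". MAS rates muscle tone "on a scale of 0, 1, 1 + , 2, 3, and 4", where "the higher the grade, the greater the muscle tone".

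The Data analysis section does not assign a method to either scale by name. Its rules are:
- A normality check: "We will check whether the data is normally distributed using the Shapiro Wilk normality test".
- A rank test when that check fails: "Nonnormal data will be tested using the Kruskal–Wallis test".
- Chi-square for a different kind of data: "Nonparametric analysis such as chi-square test will be applied for the count data, and it will be expressed as rate or composition ratio".
- Paired t-tests for change within arms, and one-way ANOVA between arms with Bonferroni-corrected post hoc comparisons.
- For time by group: "Two-factor repeated measures ANOVA will be employed to investigate the impact of within-group factors (time points) and between-patient factors (subgroups) on outcomes", with main and interaction effects.

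The Study design section schedules clinical assessments at baseline, after 2 weeks and after 6 weeks. The Conclusion lists BS and MAS among the indicators used to judge efficacy.

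**The concern.** A paired t-test or repeated measures ANOVA on grades needs a number for each grade and treats the steps as equal. BS stages at least carry an integer label. MAS does not: 1+ could be entered as 1.5, or the six grades could be numbered 0 to 5, and the article does not say which. A group-by-time result for MAS can then turn on a coding choice.

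The rank route does not fill the gap. Kruskal-Wallis compares independent groups at one time, so it can test neither change within an arm nor group by time. Used on follow-up grades, it discards the baseline grade that the trial collects. Used on change scores, it needs numeric codes again. At stake are verdicts on MAS that depend on the code, and a between-arm comparison for both scales that is weaker than the data allow.

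**Working it through.** **The plan's own figure.** The article gives no effect, distribution or power for BS or MAS. Its sample size concerns FMA-UE: 60/(1 − 0.20) = 75, rounded up to 76 for four equal arms of 19. That reproduces, and 4 × 19 is used below.

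**Which branch is reached.** In simulated data on six ordered grades with 15 or 19 per arm, Shapiro-Wilk rejected in at least one arm in 86–100% of runs, and on pooled residuals in 45–100%. The article does not say which of the two is tested. Kruskal-Wallis is therefore the usual between-arm route, but not a guaranteed one.

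**BS, assumed model.** A latent severity has person SD 1.8, logistic visit noise of scale 0.5, cut-points 1.5 apart and a common time shift of 0.4. Baseline is limited to stages 2–5, as in the Inclusion criteria. The correlation between baseline and week 2 is about 0.65. Latent arm shifts (sham, low, high, combined) are 0/0.5/0.5/1.2 in scenario 1 and 0/0.75/0.75/1.5 in scenario 2. For the repeated measures ANOVA, the week-2 shift is assumed to persist at week 6. Rejection rates at 0.05, as ranges where there were several runs:

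| Analysis of BS | No effect | Scenario 1 | Scenario 2 |
|---|---|---|---|
| Kruskal-Wallis on week-2 grades | 3.7–5.0% | 35–37% | 51–54% |
| Rank ANCOVA with baseline grade | 4.7–5.6% | 58–60% | 78–79% |
| Group-by-time ANOVA, integer codes | 4.8% | 58–59% | 80–81% |
| Proportional odds with baseline, likelihood ratio | 6.9% | 66% | 85% |

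In one set of runs, Kruskal-Wallis gave 36% and 54% against 60% and 79% for rank ANCOVA. The gaps are 60 − 36 = 24 and 79 − 54 = 25 points. Both tests use order, so the gain comes from the baseline grade. The ANOVA contains baseline as a time point and matches rank ANCOVA.

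**MAS, two codings.** The group-by-time F over three visits was computed with codes 0, 1, 1.5, 2, 3, 4 and again with 0, 1, 2, 3, 4, 5.
- With an effect, the two codings gave different verdicts at 0.05 in 9.4% of trials in one run, 10–13% in another, and 11.6% and 13.7% in a third: about 9–14%.
- Power in the first of these runs was 57% against 59%, so the code moves verdicts in both directions more than it costs power.
- With no effect, verdicts differed in 2.6% of trials (2.9% in another run). That was 45% of the trials significant under either code, so 2.6/0.45 ≈ 5.8% were significant under at least one code and 5.8 − 2.6 = 3.2% under both. The average rate for a single code is 3.2 + 2.6/2 = 4.5%, which is not inflated.
- For one-way ANOVA at a single visit, the code mattered less: 2–6% of verdicts with an effect and 1–2% without. Kruskal-Wallis on the grades does not change with the code.

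**The case against.** The strongest reply is that the plan already contains an order-respecting test, that normality will usually be rejected so that this test is used, and that the repeated measures ANOVA performs well on BS. All three statements are correct. What they leave untouched is that Kruskal-Wallis cannot serve the pre/post or group-by-time analyses, that it drops baseline when applied to follow-up grades, and that the ANOVA result for MAS still needs a code for 1+.

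A second reply is that a condensed article may leave the choice of test for each outcome, and the coding of 1+, to an analysis plan that is not shown. That lowers the priority. It does not dispose of the point, because the article does state methods for its outcomes and excepts neither scale.

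A reader might infer several stronger things that the documents do not support:
- **That every named method treats grades as numbers or as unordered categories.** Kruskal-Wallis is named and does neither.
- **That BS and MAS will go to chi-square and lose most of their power.** Chi-square is reserved for count data, and nothing assigns these scales to it. Had it been used, it would have kept 39–74% of Kruskal-Wallis power in simulation, so even then the loss exceeds half only in some settings.
- **That the repeated measures ANOVA is invalid or weak for BS.** With integer codes it rejected 4.8% under no effect and matched the rank analysis.
- **That coding 1+ produces false positives.** The 45% disagreement is a share of about 5.8% of null trials. Even an analyst who reported whichever code was significant would reject in only about 5.8%.

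**Conclusion.** The point holds in a limited form. For two ordered secondary outcomes, the plan's pre/post and group-by-time analyses have no rank or ordinal counterpart, and its rank test between arms depends on a normality test and ignores baseline when used on follow-up grades. The practical size is a MAS verdict that depends on the code in roughly one in ten trials with an effect, and about 24–25 points of power for BS if Kruskal-Wallis at week 2 is the between-arm test.

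All sizes rest on assumed grade distributions, correlation and arm shifts. The power gap will shrink if baseline and follow-up grades correlate less than assumed. That 1+ has no numeric value, and that two analyses lack an order-respecting method, needs no such assumption. Priority is low to moderate: BS and MAS are two of seven secondary outcomes, and the primary outcomes are unaffected.

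**What to change.** In the Data analysis section, add that BS and MAS are analysed as ordered grades without a prior normality test:
- **Between arms, at week 2 and at week 6:** a baseline-adjusted rank or ordinal analysis. For example, take the P value from rank ANCOVA, and report the common odds ratio with 95% CI from a proportional-odds model with arm and baseline grade. The rank P value is preferred because the likelihood-ratio test rejected 6.9% under no effect at this sample size.
- **Multiplicity:** keep the Bonferroni correction already planned for comparisons between arms.
- **Pre/post within arms:** a rank-based paired test. The sign test needs no coding. A signed-rank test ranks differences, so it would need the order codes 0 to 5 fixed in advance.

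The cost is one or two sentences, with no new data, visits or patients. The downsides are that an odds ratio is less familiar than a mean grade and rests on proportional odds, and that a P value and an interval from different models can disagree at the margin.

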This trial aims to investigate the clinical efficacy of LF-HF-rTMS on upper extremity motor function in convalescent stroke patients and to explore the mechanisms underlying its therapeutic effects. This study will assess the following: significant changes in clinical behavioral assessments and cortical excitatory parameters in patients with convalescent stroke after 10 interventions with rTMS, compared with that by sham and unilateral hemispheric stimuli. In addition, we will measure the concentrations of neuroplasticity mediators, serum BDNF, pro-BDNF, and MMP-9, and analyze their correlation with behavioral improvement.

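### The planned correlations name motor function where the stated aim is improvement, and test 11 pairs at P < 0.05 with no adjustment for arm and no error control (minor)

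*Protocol article*

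**What the plan says.** The last paragraph of the Background sets the target for serum BDNF, proBDNF and MMP-9: the trial will "analyze their correlation with behavioral improvement".

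The Data analysis section then fixes the method. It lists three sets of correlations, all Pearson:

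- "Pearson correlation analysis will be performed to investigate the correlation between cortical excitability (latency and CMCT) and motor function (FMA" (the parenthesis closes there);
- "the relationship between serum factors (BDNF, proBDNF, and MMP-9) and motor function";
- "the correlation between cortical excitability and serum factors".

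One threshold applies to everything: a P "value of < 0.05 will be regarded as statistically significant". The only multiplicity correction named is "Bonferroni correction for post hoc comparisons between groups". The section plans a Shapiro-Wilk check and a Kruskal-Wallis test for non-normal data in the group comparisons. It names no counterpart to Pearson for the correlations.

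The section does not say whether the correlated values are levels or changes, whether the four arms are pooled or analysed separately, which time point is used, or whether arm enters the analysis.

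**The concern.** Improvement and motor function are different quantities. Eligibility admits upper-limb Brunnstrom stages 2 to 5, so patients start at very different levels. A correlation of FMA-UE levels with a marker could then largely reflect severity and say little about recovery.

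The handling of arm also matters. In a four-arm trial, if treatment moves both FMA-UE and a marker, the arm means line up. A plain Pearson coefficient over all patients then picks up that alignment even when, within each arm, patients whose marker moved more did not recover more.

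Finally, many pairs are tested at an unadjusted 0.05. The Conclusion intends to explore molecular mechanisms from the electrophysiological and serum changes, so a chance or arm-driven correlation could be read as a mechanistic link.

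**Working it through.** **The plan's own figure.** The documents give no error rate or power for the correlations, so there is nothing of that kind to reproduce. The Sample size section supplies the numbers of patients: 60 / (1 - 0.20) = 75, rounded up to a multiple of four = 76, or 19 per arm. This reproduces. The checks below use n = 60 (15 per arm) and n = 76 (19 per arm).

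**Number of tests** (Data analysis section, one time point, arms pooled):

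- latency and CMCT with FMA: 2 × 1 = 2
- BDNF, proBDNF and MMP-9 with FMA: 3 × 1 = 3
- latency and CMCT with the three serum factors: 2 × 3 = 6
- total: 11

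**Chance of at least one false positive.** Tests are taken as two-sided. The Sample size section is "specified as a two-sided test with" α = 0.05; sidedness is not restated for the correlations. With independent tests and all nulls true:

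1 - 0.95^11 = 0.431.

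Simulating all 11 Pearson tests on six unrelated normal variables (20,000 runs) gives 43.4% at n = 60 and 42.9% at n = 76. The variables are unlikely to be unrelated: CMCT is calculated partly from the cortex-to-muscle conduction time, so it overlaps with latency. The documents give no correlations, so these are assumed (n = 60):

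| Latency-CMCT correlation | Correlation among serum factors | At least one false positive |
|---|---|---|
| 0 | 0 | 43% |
| 0.5 | 0.3 | 41% |
| 0.8 | 0.5 | 34% |
| 0.9 | 0.7 | 30% |

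The count depends on readings that the section leaves open. Testing at both baseline and week 2 makes 22 tests (1 - 0.95^22 = 0.676 under independence); testing separately in each arm makes 44 (1 - 0.95^44 = 0.895). A Bonferroni level of 0.05 / 11 = 0.0045 brings the simulated figure to between 3.6% and 4.9% in the 11-test scenarios.

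**Effect of pooling arms.** Assume no correlation within any arm, unit SD within arms, and arm means of 0, d/2, d/2 and d in both variables. The documents state no shift for any outcome, so d is varied. The between-arm variance is d²/8, so the expected pooled correlation is (d²/8) / (1 + d²/8). For d = 1 this is 0.125 / 1.125 = 0.11. Simulated rejection per test at 0.05 (20,000 runs):

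| d (SD) | Expected pooled r | Pooled, n = 60 | Pooled, n = 76 | Adjusted for arm |
|---|---|---|---|---|
| 0.5 | 0.03 | 5.7% | 5.7% | about 5% |
| 0.8 | 0.07 | 8.9% | 9.6% | about 5% |
| 1.0 | 0.11 | 13.6% | 15.9% | about 5% |
| 1.5 | 0.22 | 40.2% | 49.2% | about 5% |

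The inflation is slight at 0.5 SD and becomes material from about 0.8 to 1 SD in both variables.

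**Which shifts are relevant?** The section does not say which test or effect size lies behind N = 60. If it was a four-group ANOVA at 80% power, the detectable effect is f = 0.44. With the graded pattern above, that is d = 0.44 × √8 ≈ 1.25 SD in FMA-UE. Nothing in the documents says that a marker would move as far. With 1.25 SD in both variables the pooled rejection is about 24% (n = 60) to 30% (n = 76); with the marker moving half as far it is about 10% to 12%.

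**The case against.** Three stronger readings are tempting, and the text does not support them.

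- A reader might infer that raw values will be correlated over all arms. The Data analysis section says neither; both are readings of a silent text, and the pooling figures hold only if the arms are pooled.
- A reader might infer that the analysis cannot measure improvement. The Background names improvement as the target and the Conclusion speaks of changes in electrophysiology and serum factors, so motor function may simply name the construct and its scale. What can be said is that the Data analysis section does not carry the aim through.
- A reader might infer that the whole biomarker and mechanism aim hangs on these correlations. Whether a marker responds to treatment is addressed by the paired tests, ANOVA and repeated measures ANOVA, and serum BDNF is itself a primary outcome. The mechanism work is described as exploratory.

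It is also fair to object that change scores, adjustment for arm and error control in an exploratory analysis often sit in a full protocol or analysis plan that is not shown, so their mere absence here is no fault. And 43% is the independence figure, at the top of the range for 11 tests under the dependence assumed here.

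These points lower the severity and remove the unconditional wording. They do not remove the point itself. The article fixes a method (Pearson), a variable (motor function) and a threshold (0.05 throughout), and confines its correction to group comparisons. The mismatch with the Background lies within the one document, whatever another document may add.

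**Conclusion.** The concern holds in a limited form. The aim and the analysis name different quantities and need to be reconciled. As specified, the analysis is plain Pearson with no adjustment for arm and no rank alternative, and 11 pairs are tested at 0.05 without error control.

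The chance of at least one false positive is about 30% to 43%, assuming all nulls true, one test per pair and one time point; the upper end also assumes independence. Spurious association through pooling is conditional on the arms being pooled and on treatment moving both variables. It is small below about 0.8 SD and grows quickly above 1 SD, and the shifts are assumptions because the documents give none.

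Severity is minor. No efficacy conclusion depends on these correlations; what is at risk is the reading of a marker as linked to recovery.

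**What to change.** Reword the correlation paragraph of the Data analysis section to match the Background:

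- Correlate change from baseline to week 2 in each marker with change in FMA-UE over the same interval, and treat the excitability-serum pairs likewise.
- Use partial correlations adjusted for arm and baseline FMA-UE.
- Use a rank-based or log-scale version where the data are not normal.
- Report coefficients with confidence intervals and label the analysis exploratory. If significance is claimed, apply Holm or false-discovery-rate control over the 11 pairs.

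The Study design section already schedules clinical, neurophysiological and serological assessment at baseline and week 2, so no new data are needed. The cost is analysis wording, and fewer nominally significant correlations to report.
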